### Statistical methods

Normal distribution continuous variables will be presented by means and standard deviations while non-normal distribution continuous variables will be presented by medians and interquartile ranges. For categorical variables, composition ratios and 95% confidence intervals will be used to describe the variables. Chi-square analysis will be used to assess differences between the study arms in HIV testing history, HIV self-testing (HIVST) characteristics, and high-risk behaviours. Multinomial logistic regression will be used to measure the outcome of real-time monitoring equipment on medication adherence.

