### Sample size

We have powered the RCT to be able to detect meaningful changes in optimal adherence. Our estimates of outcome differences are based on our basic findings from our earlier pilot study with Chinese PrEP users, in which we found that proportions of adherence were 94% versus 86%, in intervention versus control patients after 6 months of the intervention. We will recruit 500 PrEP users per study arm. With the consideration of a two-sided alpha of 0.05 and 40% loss to follow-up of our study, we will have a 90.6% power at to detect specified differences in adherence between the two arms after intervention.

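### The stated 90.6% power belongs to a comparison of one binary proportion, not to the multinomial model named for adherence, and the deciding contrast is not stated

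*Protocol article*

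**What the plan says.** The Sample size section of the protocol article frames the target as one proportion per arm: "We have powered the RCT to be able to detect meaningful changes in optimal adherence". It takes the effect from a pilot in which "proportions of adherence were 94% versus 86%, in intervention versus control patients after 6 months", sets 500 recruits per arm with "40% loss to follow-up of our study" and a two-sided alpha of 0.05, and concludes that "we will have a 90.6% power at to detect specified differences in adherence between the two arms after intervention".

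Table 3 (Study endpoints) sorts each adherence measure into three ordered classes: high (90% or more), intermediate (60% to below 90%) and low (below 60%).

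The Statistical methods section names one method for the effect on adherence: "Multinomial logistic regression will be used to measure the outcome of real-time monitoring equipment on medication adherence". The chi-square test, which would fit a comparison of two proportions, goes elsewhere: "Chi-square analysis will be used to assess differences between the study arms in HIV testing history", together with self-testing characteristics and risk behaviours. None of these is an endpoint in Table 3.

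**The concern.** A power statement is useful only if it describes the test that will decide the trial. Here the power calculation has one parameter, the difference between two proportions. The named model has two treatment parameters, for example intermediate versus high and low versus high, and makes no use of the order of the classes.

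Two things are at stake. The first is that the advertised 90.6% may not describe the analysis that is run. The second is that two odds ratios can point to different conclusions. With no stated rule, the choice between them, or between either of them and an overall test, could be made after the results are seen.

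**Working it through.** **Inputs from the Sample size section.** 94% versus 86%; 500 recruited per arm; 40% loss, so 500 × 0.60 = 300 evaluable per arm; two-sided alpha 0.05.

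**Step 1: reproduce the stated power.** Pooled two-proportion z-test, mean proportion 0.90:
- s₀ = √(2 × 0.90 × 0.10 / 300) = 0.02449
- s₁ = √(0.94 × 0.06 / 300 + 0.86 × 0.14 / 300) = 0.02428
- power = Φ[(0.08 − 1.96 × 0.02449) / 0.02428] = Φ(1.318) = **90.6%**

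This matches the stated figure. The calculation is that of a single binary proportion.

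**Step 2: what the named model needs.** With three classes it needs three expected proportions per arm. The article gives none. I take the high class as 94% versus 86% (an assumption, see the objection), so that 6% and 14% remain, or 18 and 42 people out of 300. How these divide into intermediate and low is also an assumption, so I vary it.

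**Step 3: overall 2-df test.** The Pearson noncentrality is λ = n Σ (p₁ⱼ − p₂ⱼ)² / (p₁ⱼ + p₂ⱼ), and the power is P[χ²₂(λ) > 5.99]. For intermediate/low of 4/2% versus 9/5%:

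λ = 300 × (0.0064/1.80 + 0.0025/0.13 + 0.0009/0.07) = 10.7, giving 84.2%.

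The likelihood-ratio version (LR) uses its own noncentrality.

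**Step 4: single contrasts.** These are Wald tests of each log odds ratio against the high class, each at two-sided 0.05, by simulation (accurate to about one percentage point). A trial with an empty low cell counts as not significant for low versus high.

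| Intermediate/low, intervention vs control | 2-df power, Pearson / LR | Intermediate vs high | Low vs high | Both significant | Exactly one significant |
|---|---|---|---|---|---|
| 4/2 vs 9/5 | 84.2% / 85.2% | 74% | 55% | 41% | 47% |
| 3/3 vs 7/7 | 84.1% / 85.1% | 65% | 66% | 44% | 44% |
| 5/1 vs 11/3 | 84.6% / 85.7% | 80% | 35% | 28% | 59% |
| 5/1 vs 9/5 | 89.6% / 91.4% | 53% | 81% | 43% | 47% |
| 5/1 vs 7/7 | 95.2% / 96.9% | 22% | 93% | 21% | 74% |

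In the first three rows the split is the same or nearly the same in both arms; in the last two it differs between arms. With 1% low in the intervention arm, the chance of an empty low cell there is 0.99³⁰⁰ = 4.9%.

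**Step 5: sample-size equivalent.** With the same split in both arms, the 2-df likelihood-ratio test reaches 90.6% at about 355 evaluable per arm. That means 355/0.60 = 592 recruited at 40% loss, or a loss of 1 − 355/500 = 29% with the planned 500.

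**The case against.** Powering on a simple proportion and then analysing with a regression model is common, and an article may leave the choice of contrast to a fuller document. Four more specific objections carry weight.

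- **The model contains the powered comparison.** With arm as the only covariate, a multinomial model reproduces the observed class proportions exactly. The difference in the probability of high adherence can be read from it, with power Φ(0.08/0.02428 − 1.96) = 90.9% (unpooled). A reader might infer that the powered hypothesis has no planned test. The article does not support that; what it lacks is a statement that this contrast is the one that counts.
- **The shortfall is not fixed.** A reader might infer that the named analysis falls short of 90.6%. That depends on a split that the article does not give, and the last row of the table exceeds 90.6% on either version of the test.
- **Two links are inferred.** The article does not equate optimal adherence with the class of 90% or more, and does not say that the three classes are the model's response. They are, however, the only adherence categories it gives.
- **The low single-contrast figures matter only if a single contrast decides.** No sentence says that one does.

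All four stand as limits on the claim. They do not remove the mismatch, because the article states both the power and the model and connects them nowhere. The splits that favour the overall test do not settle the matter either: in those two rows the odds ratios still disagree on significance in 47% and 74% of simulated trials.

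Whether a proportional-odds model would suit the ordered classes better, and whether the chi-square comparisons should stay, are matters of preference and not part of this point.

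**Conclusion.** The point holds in a limited form. The 90.6% is correct for a binary comparison of 94% versus 86% with 300 evaluable per arm. It was not derived for the multinomial model, and the power of that model cannot be derived from the stated inputs.

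The size of the gap rests on the assumed splits and on reading high adherence as the powered proportion. With similar splits in both arms, the overall test loses about 5 to 6 points (84-86%) and the single contrasts have about 35-80% power. With splits that differ between arms, the overall test can match or exceed the stated figure. It does not follow that the trial is underpowered.

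The firmer consequence is the missing decision rule. Across the five splits, if the assumed effect is true, exactly one of the two odds ratios is significant in about 44-74% of trials, and nothing in the article says which one decides.

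**What to change.** Preferred: state in Statistical methods that the primary analysis compares the proportion with optimal adherence at 6 months between arms, as a risk difference with 95% CI. Give the cut-off explicitly: for example the class of 90% or more, if that is what the pilot's 94% and 86% refer to. Keep the three-class model as a secondary analysis. The stated power then applies as written.

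Alternative: if the three-class model is to remain primary, name the overall test or contrast that decides, state the expected proportions in all three classes for each arm, and restate the power on that basis.

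Either way the cost is a few sentences, settled before analysis, with no change to data or sample size. The downside is small: the three-class result becomes secondary, or the stated power may become somewhat less favourable.

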### Ethics and dissemination

Written informed consent will be provided to all study participants before take part in this study. The study was approved by the First Affiliated Hospital of China Medical University Ethics Review Committee ([2019]2019–253-3).

## Discussion

Traditional methods of measuring medication adherence such as self-report and pill counting are executed intermittently or at the end of the study period, often several months after the dosage has been missed. Accordingly, these methods often cannot guide intervention before the disease recurs or worsens. Hence, the ability to change medication adherence and prevent treatment failure or drug resistance with these methods is limited. In contrast, EDM is characterised by real-time monitoring and data processing, which allow healthcare teams and family members to monitor medication adherence and send reminders just-in-time to patients who have missed doses, before the disease may worsen. EDM is therefore a more efficient strategy to improve medication adherence.

Medication adherence is crucial for achieving optimal benefits from PrEP. However, many participants over-report PrEP medication adherence by traditional approaches such as self-reporting and pill counting, which adds to the challenge of accurately measuring medication adherence [15]. With traditional approaches, measurement of adherence after doses have been missed leads to an inability to provide timely intervention and thus to worse adherence. Real-time monitoring technology creates the ability to monitor medication adherence between routine visits and can trigger just-in-time intervention before adherence has lapsed for a substantial amount of time. Our study will be the first to directly compare traditional measurement of adherence versus real-time monitoring with just-in-time individualised intervention in PrEP users.

This study is focused on a novel, individualised behaviour intervention to reduce the risk of decreased medication adherence among PrEP users in China. Ours will be the first study of this type of intervention for improvement of PrEP medication adherence. Just-in-time telephone intervention requires investment of more time and energy. Our intervention employs novel technology combined with just-in-time SMS medication reminders and individualised telephone intervention to increase the intensity and efficiency of improving PrEP medication adherence in real time. Furthermore, telephone intervention only focuses on those with a missed dosage after just-in-time SMS reminders which can save time and energy. The control group will receive weekly universal undifferentiated SMS medication reminders since the real-time medication condition is unknown. Clinicians can provide just-in-time professional intervention based on information from the back-end real-time monitoring platform to improve the efficacy of PrEP in preventing the transmission of HIV infection. Dose-to-dose medication adherence data and curves generated on adherence patterns are informative in promoting self-management and intervention from others who are engaged with participants. The study has several important strengths, including capitalizing on the infrastructure of a large-scale, real-world multicentre study in China, use of real-time monitoring devices with just-in-time intervention to advance medication adherence, and measure the efficacy of such devices compared to traditional approaches.

Our study tests a real-time monitoring device with just-in-time intervention against other traditional approaches to address medication adherence in PrEP users. We hypothesize that by targeting real-time monitoring and intervention to reduce the risk of viral rebound, our strategy will improve TDF/FTC medication adherence, allowing clinicians and family members to maintain confidence regarding adherence.

Our study should be evaluated considering several limitations. First, the *CROPrEP* project is focused on the MSM population, in which medication adherence characteristics may be different from other patient populations. It has been shown that research study participants generally exhibit higher medication adherence levels than other clinical patients [20]. Accordingly, we recommend that future studies be conducted in other key populations to validate the effects of real-time monitoring and just-in-time intervention on PrEP medication adherence. In addition, the cost of real-time monitoring devices has limited their large-scale uptake in research and general clinical care. Thus, development of low-cost versions of these devices will be critically important for their future application.

## Data Availability

Not applicable.

## Abbreviations

PrEP: Pre-exposure prophylaxis
MSM: Men who have sex with men
TDF/FTC: Tenofovir disoproxil fumarate/emtricitabine
SMS: Short Messaging Service
ART: Antiretroviral therapy
EDM: Electronic drug monitors
HIVST: HIV self-testing
